## Figures and Tables

**Table 1 metabolites-13-00182-t001:** Primary and secondary outcome measures. BMI: body mass index; BP: blood pressure; CRP: C-reactive protein; DASS: Depression, Anxiety, and Stress Scale; fGlc: fasting glucose; HDL-c: high-density protein cholesterol; MADRS: Montgomery–Åsberg Depression Rating Scale; MC: microbiota composition; MDA: malondialdehyde; SCFAs: short-chain fatty acids; TAC: total antioxidant capacity; TG: triglycerides; WBC: white blood cells; WC: waist circumference; WHOQOL-BREF: The World Health Organization Quality of Life-BREF.

	Materials and Methods			
	Psychometric Tools	Biological Samples		Physical Examination
		Blood	Feces	
Primary outcome measures				
Depressive symptoms	MADRS			
Secondary outcome measures				
Anxiety symptoms	DASS			
Stress level	DASS			
Quality of life	WHOQOL-BREF			
Metabolic parameters		fGlc, HDL-C, TG		BP, BMI, WC
Microbiota function			MC, SCFAs	
Inflammations parameters		WBC, NEU, CRP		
Oxidative stress parameters		TAC, MDA		

**Table 2 metabolites-13-00182-t002:** Depressive disorders in the ICD 11.

Depressive Disorders in the ICD 11	Code
Single-episode depressive disorder	6A70
Recurrent depressive disorder	6A71
Dysthymic disorder	6A72
Mixed depressive and anxiety disorder	6A73
Other specified depressive disorders	6A7Y
Depressive disorders, unspecified	6A7Z

**Table 4 metabolites-13-00182-t004:** The list of the recent clinical trials that demonstrated the efficacy of *Bifidobacterium longum* and *Lactobacillus helveticus* toward depressive, anxiety, and stress symptoms.

The List of the Recent Clinical Trials That Demonstrated the Efficacy of *Bifidobacterium longum* and *Lactobacillus helveticus* toward Depressive, Anxiety, and Stress Symptoms				
The Authors	Animal/Human Studies	Duration	Population	Results
Kazemi et al., 2018 [53]	Humans	8 weeks	110 depressed patients	”A significant decrease in BDI score (17.39–9.1) compared to the placebo (18.18–15.55) and prebiotic (19.72–14.14) supplementation (*p* = 0.042)”.
Romijin et al., 2017 [54]	Humans	8 weeks	79 participants (10 dropouts) with at least moderate scores on self-report mood measures	No significant impact on any psychological outcome measure.
Messaoudi et al., 2011 [50]	Animals (rats) and humans	4 weeks	66 participants based on a score of ≤12 in the HADS-anxiety subscale (HADS-A) and the HADS-depression subscale (HADS-D) and equal to or less than 20 in the HADS total score on the initial examination	A significant reduction in anxiety-like behavior in rats (*p* < 0.05) and alleviated psychological distress in volunteers, as measured particularly by the HSCL-90 scale, HADS, and CCL.
Pinto-Sanchez et al., 2017 [56]	Humans	6 weeks	44 adults with IBS and diarrhea or a mixed-stool pattern (based on the Rome III criteria) and mild-to-moderate anxiety and/or depression (based on the Hospital Anxiety and Depression Scale)	14 of 22 patients in the BL (Bifidobacterium longum) group had a reduction in depression scores of 2 points or more on the Hospital Anxiety and Depression Scale vs. 7 of 22 patients in the placebo group (*p* = 0.04). BL had no significant effect on anxiety or IBS symptoms.
Arseneault-Bréard et al., 2012 [51]	Animals (rats)	-	-	”Probiotics reversed the behavioural effects of myocardial infarction (MI) (*p* < 0.05), but did not alter the behaviour of sham rats. Intestinal permeability was increased in MI rats and reversed by probiotics. In conclusion, L. helveticus R0052 and B. longum R0175 combination interferes with the development of post-MI depressive behaviour and restores intestinal barrier integrity in MI rats.”
Diop et al., 2008 [55]	Humans	3 weeks	75 healthy volunteers with symptoms of stress	Significant reduction in 2 stress-induced gastrointestinal symptoms (abdominal pain and nausea/vomiting) and no significant modification of the other physical and psychological symptoms and sleep problems.
Gilbert et al., 2012 [52]	Animals (rats)	-	-	”administration of probiotics, starting after the onset of reperfusion, are beneficial to attenuate apoptosis in the limbic system and post-MI depression in the rat”.

## Data Availability

Data sharing is not applicable.

## Appendix A

Sample size analysis details:

The authors made an effort to determine the correct sample size for the study regarding the secondary endpoints.

As for CRP, the investigators in this study decided to use the number of participants needed to detect a mean difference between the groups in the hsCRP level of 2.0 mg/L (standard deviation 3.0 mg/L) at day 60 with 80% power and 95% confidence. The number of subjects needed was 20 per group. The range of values for the mean CRP and standard deviation in the group of depressed patients was indicated in the studies by Chamberlain et al. and Pitharouli et al. [76,77].

As for BMI, the sample size calculations were based on the assumption of a 2.0 kg/m^2^ reduction in BMI at day 60 in the probiotic group compared with the placebo group (M1 = 23.0, M2 = 21.0). A decrease in BMI by approximately 2 kg/m^2^ may significantly influence metabolic risk [78]. To detect this difference, assuming a common standard deviation of 3.0 using a two-group *t*-test with a 0.05 two-sided significance level, we estimated that a sample size of 20 subjects in the probiotic intervention group and 20 subjects in the placebo group would have 80% power.

As for the lipid profile, we determined that 16 participants in each study group (probiotic versus placebo) would be sufficient to detect a mean difference in LDL cholesterol of 0.45 mmol/L (M1 = 3.45 mmol/L, M2 = 3.0 mmol/L, SD = 0.6 mmol/L), with 80% power at *p* = 0.05. Hypothetical values were based on the data found in the study by Ivey et al. [79].

As for the first criterion of metabolic syndrome, namely, WC, we used a standard deviation of 8.5 and a difference in mean of 9.0 (M1 = 90.0 cm, M2 = 99.0 cm). We based our assumptions on a study by Niyonsenga et al. [80], which indicated a mean and standard deviation of WC in a depressed population. This calculation determined that 16 patients for each group were required to provide >80% power with *p* = 0.05.

As for HDL, we used a standard deviation of 11.6 and a difference in mean of 12.0 (M1 = 67.0 mg/dL, M2 = 55.0 mg/dL). We based our assumptions on a study by Martinac et al. [81], which provided a mean and standard deviation of HDL in a depressed population. This calculation determined that 16 patients for each group were required to provide >80% power with *p* = 0.05.

As for TG, we used a standard deviation of 39.0 and a difference in mean of 40.0 (M1 = 180.0 mg/dL, M2 = 140.0 mg/dL). We based our assumptions on a study by Martinac et al. [81], which provided the mean and standard deviation of TG in a depressed population. This calculation determined that 16 patients for each group were required to provide >80% power with *p* = 0.05.

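### Appendix A understates the per-group sizes needed for 80% power for CRP, BMI and LDL (20, 20, 16 against 37, 37, 29); the planned 50 per group remains sufficient, and LDL is not an outcome of the trial

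*Protocol article*

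**What the plan says.** The Sample Size Calculation section sizes the trial on MADRS at about 100 patients, 50 per group, and refers to Appendix A for the secondary outcome measures. Appendix A then gives six calculations. Three matter here.

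- **CRP:** the target effect is given as "mean difference between the groups in the hsCRP level of 2.0 mg/L (standard deviation 3.0 mg/L) at day 60". Power is set at 80% and confidence at 95%. The result is "The number of subjects needed was 20 per group".
- **BMI:** the assumed means are 23.0 and 21.0, "assuming a common standard deviation of 3.0 using a two-group *t*-test with a 0.05 two-sided significance level". The result is "20 subjects in the probiotic intervention group and 20 subjects in the placebo group would have 80% power".
- **LDL:** "16 participants in each study group (probiotic versus placebo) would be sufficient to detect a mean difference in LDL cholesterol of 0.45 mmol/L", with means 3.45 and 3.0 mmol/L, SD 0.6 mmol/L, 80% power and p = 0.05.

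The other three calculations (waist circumference, HDL, triglycerides) each give 16 per group for more than 80% power.

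LDL appears only in this appendix. The outcome list in the Introduction, the blood tests in sections 2.2 and 3.2, and Table 1 name HDL cholesterol and triglycerides as the lipids.

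**The concern.** All three calculations describe a comparison of two independent groups, and for BMI the appendix names the test, the sidedness and the level outright. A standardised difference of 2.0/3.0 = 0.67 is moderate, and 20 per group is too few to detect it with 80% power.

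The appendix is also inconsistent with itself. It gives 16 per group both for LDL, with a standardised difference of 0.75, and for triglycerides, with 40/39 = 1.03, at the same power and level. Required size varies roughly with the inverse square of the standardised difference, so LDL should need about (1.026/0.75)² ≈ 1.9 times as many patients.

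What is at stake is the accuracy of published size and power figures for secondary endpoints. Anyone who takes 20 evaluable patients per group as enough for CRP or BMI would have little better than an even chance of detecting the assumed effect. The LDL calculation raises a separate matter: it supports no endpoint that the trial lists or plans to measure.

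**Working it through.** **Inputs (Appendix A).** CRP: difference 2.0, SD 3.0. BMI: difference 23.0 − 21.0 = 2.0, SD 3.0. LDL: difference 3.45 − 3.0 = 0.45, SD 0.6. Power is 80% and alpha 0.05. Two-sidedness is stated for BMI; for CRP and LDL it is the usual reading. Allocation is 1:1 (Randomization section).

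**Standardised differences.** d = difference/SD: CRP and BMI 0.667, LDL 0.75.

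**Trying to reproduce the stated sizes.** The two-sample normal approximation is n per group = 2(1.960 + 0.842)²/d², with (1.960 + 0.842)² ≈ 7.849.

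- CRP and BMI: 2 × 7.849/0.4444 = 35.3, so 36.
- LDL: 2 × 7.849/0.5625 = 27.9, so 28.

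The exact (noncentral t) calculation, with the alternatives that might explain the stated figures:

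| Calculation | CRP, BMI | LDL |
|---|---|---|
| Stated in Appendix A | 20 | 16 |
| Two-sample t, two-sided | 36.3 → 37 | 28.9 → 29 |
| Two-sample t, one-sided | 28.5 → 29 | 22.7 → 23 |
| One-sample or paired t, two-sided | 19.67 → 20 | 15.98 → 16 |

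No two-sample variant returns the stated sizes. The two-sided one-sample (paired) t-test returns all three exactly.

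**Power at the stated sizes.** The noncentrality is d√(n/2).

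- CRP and BMI at 20 per group: 0.667 × √10 = 2.11. Power is 53.8% by t-test and 55.9% by normal approximation.
- LDL at 16 per group: 0.75 × √8 = 2.12. Power is 53.7% by t-test and 56.4% by normal approximation.
- A one-sided test at these sizes would still give only about 66% to 68%.

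**Control: the other figures.** The two-sample t-test gives the following.

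- Waist circumference: d = 9.0/8.5 = 1.06, n = 15.03, so 16 (82.6% power at 16).
- HDL: d = 12.0/11.6 = 1.03, n = 15.69, so 16 (80.8%).
- Triglycerides: d = 40/39 = 1.03, n = 15.94, so 16 (80.2%).
- MADRS: d = 2.9/5.15 = 0.563; 50 per group gives 80.4% by normal approximation and 79.6% by t-test.

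All of these agree with what the article states.

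**Power at the planned 50 per group.** The noncentrality d√25 is 3.33 for CRP and BMI and 3.75 for LDL. Power by t-test is 91.0% for CRP and BMI and 96.0% for LDL.

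**The case against.** The strongest reply is that nothing in the conduct of the trial depends on these figures. Enrolment comes from MADRS, 50 per group exceeds every corrected size, and power for the assumed CRP and BMI effects at that size is above the advertised 80%. This stands, and it is why the point is minor.

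Several stronger readings are tempting, but the documents do not support them.

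- **That the trial is underpowered for these endpoints.** The 54% belongs to a trial of 16 to 20 per group, which is not the one planned.
- **That the appendix claims a comfortable size or a margin against dropout.** It says only that an effort was made to find the correct size for the secondary endpoints. It states no attrition allowance, and the Discussion lists a possibly insufficient patient population as a limitation.
- **That a one-sample formula was used.** The match is exact for all three figures, but the article names no such formula. The origin is an inference, and the figures are wrong whatever it was.
- **That LDL's absence leaves a lipid endpoint without a calculation.** HDL and triglycerides, the lipids actually listed, have their own calculations, and these reproduce.

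Two technical defences fail. Sidedness is unstated for CRP and LDL, but one-sided testing would still need 29 and 23 per group. Baseline adjustment could lower the required size, but it would take a baseline correlation of about 0.65. The appendix states neither adjustment nor a correlation, and for BMI it specifies a plain two-group t-test.

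**Conclusion.** The point holds as an error in stated figures. On the appendix's own inputs, 80% power needs 37 per group for CRP, 37 for BMI and 29 for LDL by two-sided two-sample t-test at 5%. The stated 20, 20 and 16 fall short by 17, 17 and 13 and give about 54% power. The result is firmest for BMI, where test, sidedness and level are all written down; for CRP and LDL it assumes the usual two-sided 5% test, and a one-sided test does not rescue them. The choice between t-test and normal approximation moves the required sizes by one patient per group.

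Separately, the LDL calculation relates to a variable that is neither listed as an outcome nor included in the blood tests.

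Severity is minor: the planned size, the primary endpoint and its analysis are unaffected.

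**What to change.** In Appendix A:

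- **CRP and BMI:** replace 20 by 37 per group, name the method (two-sided two-sample t-test at 5%), and state that 50 per group gives about 91% power for the assumed effects.
- **LDL:** delete the calculation. Only if LDL is added to both the outcome list and the blood panel should it be kept, corrected to 29 per group, with 96% power at 50 per group.

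The cost is a text correction, with no extra patients and no change to the analysis. Keeping LDL would add one assay on blood that is already being drawn.
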